# Protocol for a pilot randomised controlled clinical trial to compare the effectiveness of a graduated three layer straight tubular bandaging system when compared to a standard short stretch compression bandaging system in the management of people with venous ulceration: 3VSS2008

**DOI:** 10.1186/1745-6215-11-26

**Published:** 2010-03-09

## Abstract

**Background:**

The incidence of venous ulceration is rising with the increasing age of the general population. Venous ulceration represents the most prevalent form of difficult to heal wounds and these problematic wounds require a significant amount of health care resources for treatment. Based on current knowledge multi-layer high compression system is described as the gold standard for treating venous ulcers. However, to date, despite our advances in venous ulcer therapy, no convincing low cost compression therapy studies have been conducted and there are no clear differences in the effectiveness of different types of high compression.

**Methods/Design:**

The trial is designed as a pilot multicentre open label parallel group randomised trial. Male and female participants aged greater than 18 years with a venous ulcer confirmed by clinical assessment will be randomised to either the intervention compression bandage which consists of graduated lengths of 3 layers of elastic tubular compression bandage or to the short stretch inelastic compression bandage (control). The primary objective is to assess the percentage wound reduction from baseline compared to week 12 following randomisation. Randomisation will be allocated via a web based central independent randomisation service (nQuery v7) and stratified by study centre and wound size ≤ 10 cm^2 ^or >10 cm^2^. Neither participants nor study staff will be blinded to treatment. Outcome assessments will be undertaken by an assessor who is blinded to the randomisation process.

**Discussion:**

The aim of this study is to evaluate the efficacy and safety of two compression bandages; graduated three layer straight tubular bandaging (3L) when compared to standard short stretch (SS) compression bandaging in healing venous ulcers in patients with chronic venous ulceration. The trial investigates the differences in clinical outcomes of two currently accepted ways of treating people with venous ulcers. This study will help answer the question whether the 3L compression system or the SS compression system is associated with better outcomes.

**Trial Registration:**

ACTRN12608000599370

## Background

Venous disease is the most common cause of leg ulcers [1,2]. The refractory nature of venous ulcers affects the quality of life and work productivity of those persons afflicted [3]. This, in combination with the high costs of long-term therapy, makes venous ulcers a major health problem in developed countries. Management of venous leg ulcers is based on understanding pathophysiologic abnormalities [4,5]. Compression increases ulcer healing rates compared with no compression. Multi-layered systems are more effective than single-layered systems[6] High compression is more effective than low compression but there are no clear differences in the effectiveness of different types of high compression[6].

The short stretch compression system is often used as a standard treatment in mainland Europe and Australia. It is an inelastic bandage that has minimal extensibility when applied[7]. The main disadvantage of short stretch bandages is that they tend to become loose after a few hours of wear time and tend to slip down the leg[8]. Short stretch bandage application also requires the skill of experienced health care professionals[7] whereas elastic tubular bandages can be applied by patients and carers[8].

Application of the 3L elastic tubular system is very simple; it can be applied in minutes and does not require a trained health professional. The short stretch bandage needs to be applied by a trained practitioner and takes longer to apply. In some instances if applied incorrectly can cause damage to underlying tissues on the lower limb. In view of recent literature [9] that has demonstrated that community nurses were unwilling to use compression bandages because they were uncertain of which type of compression bandage to use, and also how to apply bandages. The 3L elastic compression system may be more acceptable to nurses who apply compression. The 3L elastic system may also increase the number of patients in the community who are willing to wear compression. There is evidence that some patients with venous ulcers have increasing difficulty in complying to compression bandaging[10]. The reasons for and determinants of non-adherent behaviour to compression is multifactorial and include pain, discomfort and lack of valid lifestyle advice by healthcare professionals [11].

The aim of this study is to compare the efficacy and safety of two high compression bandages in healing venous ulcers in patients with chronic venous ulceration; graduated three layer straight tubular bandaging (3L) compared to standard short stretch (SS) compression bandaging. The 3L compression bandage is easy to apply, needs little, if any, training to apply to the limb, is well tolerated by patients and is cost effective.

### Venous leg ulcer Incidence

Chronic leg ulcers are leg ulcers which have not healed themselves in a four week period. Chronic leg ulcers affect 1% of the general population in Australia [4], and 3.6% of people older than 65 years [5].

Venous ulceration represents the most prevalent form of difficult to heal wounds and these problematic wounds require a significant amount of health care resources for their treatment. The incidence of venous ulceration is rising with the increasing age of the general population. The most common cause of lower extremity ulcers is venous insufficiency and accounts for nearly 80% of all ulcers [12,13].

Risk factors for development of venous ulcers include venous disease, obesity, immobility, phlebitis, family history of varicose veins, deep vein thrombosis, previous surgery for varicose veins and congestive cardiac failure. Up to 50% of patients with chronic venous insufficiency have a history of leg injury [12,13].

### Aetiology of venous ulcers

The pathophysiology of venous ulceration is controversial [13] however it is believed that ulcers result from venous occlusion or valvular incompetence and subsequent superficial venous hypertension [14]. Venous leg ulcers occur as a result of underlying venous disease where damage has occurred to the superficial deep or perforating veins. Although aetiology of venous ulceration is unclear, it has been suggested that ulceration results from increased intraluminal pressure in the capillaries. This results in fibrin deposition around the capillaries [15]. White blood cells are activated and release proteolytic enzymes that cause further tissue destruction. The alternative 'Trap' hypothesis proposes that fibrin and macromolecules eventually leak into the dermis where they bind with growth factors, making then unavailable for the tissue repair process.

The most recent theories about pathogenesis of venous ulcer have associated it with microcirculatory abnormalities and generation of an inflammatory response. The molecular and cellular profiles of chronic skin wound wounds are substantially different than found in acute healing wounds. Healing time is influenced by patient age, ulcer duration and ulcer area, but not by type of venous incompetence [15,16]

### Diagnosis of venous ulcers

In most instances, diagnosis of venous ulceration may be made using clinical criteria alone; however in 25% of cases leg ulcers will have mixed characteristics. The ankle-brachial index is a common vascular assessment to determine underlying aetiology although the gold standard in evaluating venous disease is considered to be colour duplex ultrasonography [17]. More commonly, the ankle-brachial index is measured using a Doppler to exclude arterial disease.

### Treatment of venous ulcers

The mainstay treatment of leg ulcers is sustained graduated high compression bandaging of the affected limb [18]. This acts by reducing the abnormally high pressure seen in the superficial veins and underlying lower limb swelling and oedema. Healing can be expedited through elevation of the affected limb, improved mobility, weight reduction, and improved nutrition. High compression bandaging systems may be delivered using either elastic or inelastic bandaging. A recent meta-analysis of bandaging systems found that multilayer compression bandages seemed to be superior to single-layer bandages in promoting ulcer healing [18]. Based on current knowledge the multi-layer high compression system is described as the current gold standard for treating venous ulcers. However, to date, despite our advances in venous ulcer therapy, no convincing low cost compression therapy studies have been conducted. And although we know that high compression is more effective than low compression there are no clear differences in the effectiveness of different types of high compression.

### Venous ulcer healing

Venous leg ulcer healing rates vary considerably. In wound centres providing graduated compression bandaging treatment for venous ulcers, healing rates vary from 25 to 50% after 12 weeks to 40% - 70% at 12 weeks [19] and after two years of compression therapy 20% of all chronic venous leg ulcers remain unhealed and even when healing does occur, approximately 56% will recur [3].

There are many reasons for variation in treatment times for venous ulcers. Chronic wounds that measure less than 10 cm^2 ^and are present for less than 12 months at first treatment are likely to be healed in 71% of patients within 24 weeks of treatment [20]. Conversely, chronic wounds that were greater than 10 cm^2 ^and have been present for more than 12 months, had only a 22% likelihood of being healed within the 24 week period. High compression is more effective than low compression but there are no clear differences in the effectiveness of different types of high compression [18].

### Economic and personal burden of venous ulcers

The impact of leg ulcers is felt both in physical suffering and reduced quality of life of those affected and in financial costs to the community [21]. Analysis performed more than ten years ago in Australia estimated that venous ulcers were responsible for about $400 million annually in health care costs. The high prevalence of venous ulcer has a significant socioeconomic impact in terms of medical care, days off work and reduced quality of life [4]. Treatment of venous ulcers is both time consuming and costly. Most of this cost is associated with the supply of dressings including multi layer bandages and community nurse visits [17].

The projected cost of management of venous ulcers is significant. Currently, up to 20 per 1000 individuals over the age of 80 have an active leg ulcer. One in eight Australians are aged over 65 years. By 2044 those aged over 65 years will account for one in four Australians. The expected number of people aged over 65 years living in western societies is anticipated to double within the next 40 years or so. Because the cost and resource implication of management of venous ulcers will cause considerable strain on the health system, strategies to improve management and cost effectiveness of this condition must be seen as a priority. Leg ulceration is a chronic condition, the prevalence of which is likely to increase as populations age [22]. Leg ulcers are reported as having an impact on virtually every aspect of daily life: pain is common, sleep is often impaired, mobility and work capacity tend to be restricted, personal finances are often adversely affected [23], and social activities are restricted due to fear of injury and negative body image [24].

Chronic venous ulcer healing remains a complex clinical situation and often requires the intervention of skilled, but costly multidisciplinary wound care teams. Venous leg ulcers that have been present for a prolonged period of time pose a substantial management challenge for clinicians. Traditional treatment options have often been ineffective or associated with several drawbacks. Although multi layer compression therapy is the standard care provided for management of venous leg ulcers, we are still unsure of the optimum level of compression needed to heal venous ulcers. There is a need to assess the healing efficacy of the two compression bandaging systems in the management of people with venous ulceration. The three layer compression system is cheaper alternative and may improve potential for patients to tolerate and comply with wearing compression bandages.

## Methods/Design

### Rationale for Conducting the Trial

This pilot study is being conducted to assess the healing efficacy and safety of a graduated three layer straight tubular bandaging system when compared to standard compression bandaging system in the management of people with venous ulceration. Indications of increased venous ulcer healing efficacy of the 3 layer compression system may provide a basis for greater compliance from patients and therefore improve healing rates. As an easy to apply, economical compression system this intervention may be a useful treatment for people with venous ulcers. We plan to recruit sufficient numbers at each site to test recruitment strategy and recruitment rate to inform a national study.

### Summarized Details of Investigational Products

The Investigational Product being studied is *Tubular - Form*; an elastic tubular bandage. Tubular form is listed with TGA (AUST L 59144) as a treatment for varicose conditions and control of oedema. In this study the investigational product will be used in graduated lengths of 3 layers of the tubular bandage system as follows:

1. from base of toes to just under knee (long layer)

2. from base of toes to above calf pump (medium layer)

3. from base of toes to mid gaiter (short layer)

The control group will be treated with standard short stretch compression therapy which consists of:

1. a padding layer

2. inelastic short stretch compression bandage

3. a tubular stocking

All layers of standard compression therapy will be applied from base of toes to just under the knee.

### Objectives

#### Hypotheses

##### Null Hypothesis

There is no difference in wound size reduction with graduated three layer straight tubular bandaging system when compared to standard short stretch compression therapy bandage.

##### Alternative Hypothesis

There is a difference in wound size reduction with graduated three layer straight tubular bandaging system when compared to standard short stretch compression therapy bandage.

#### Primary Outcome

The percentage reduction of wound area from baseline compared to week 12 following randomisation. The size of the wound area will be measured by Visitrak wound measurement system and wound digital photographs.

#### Secondary Outcomes

1. The proportion of ulcers healed within the trial period. (Complete healing is defined as full 100% epithelialisation or skin closure without drainage)

2. The incidence of treatment related adverse events

3. Reliability and acceptability (withdrawals)

4. Number of adverse effects and serious adverse events

5. Quality of Life measures at baseline, at end of treatment and at 3 month follow up (SF 36 and Cardiff Wound Impact Schedule (CWIS))

6. Self-reported compliance of compression bandage

7. Recurrence rates.

### Participant Selection

#### Type, Source and Number of Participants

Forty six participants will be recruited into the study from speciality wound clinics. Attendance at the clinics is by referral for clinical advice and management from General Practitioners or community nurses.

Study participants will be aged over 18 years of age, and will have a venous ulcer that is confirmed by CEAP clinical assessment to be the result of chronic venous insufficiency. Venous disease can be classified according to severity, cause and specific abnormality using the CEAP classification. Use of such a classification improves the accuracy of the diagnosis. The elements of CEAP classification are: **C**linical severity, **E**tiology or cause, **A**natomy and **P**athophysiology.

Participants may have multiple ulcers but only ONE will be considered to be the target ulcer. This will be the largest ulcer (between 1 cm^2 ^and 20 cm^2^) and separated from other ulcers by at least 2 cm.

Potential study participants will be provided with a study information sheet and asked to sign an Informed Consent Form. Following this, a formal assessment will be undertaken by a research nurse to determine eligibility according to the following inclusion and exclusion criteria.

##### Inclusion Criteria

Male and female study participants who meet all of the following criteria can be entered into the study:

1. Presence of a venous ulcer that is confirmed by CEAP clinical assessment to be the result of chronic venous insufficiency

2. Aged over 18 years

3. Present with clinical evidence of chronic venous insufficiency and chronic venous ulceration as evidenced by one or more of the following:

i. lower limb pigmentation

ii. varicose eczema

iii. lipodermatosclerosis

iv. varicose veins

4. Chronic venous leg ulcer (target ulcer) that

i. Has been present for at least 4 weeks

ii. is of an area equal to or greater than 1 cm^2 ^but less than or equal to 20 cm^2 ^as measured by digital planimetry techniques

5. Ankle Brachial Pressure index of equal or greater than 0.8 mmHg

6. Ankle circumference of greater than 20 cm and less than 30 cm

7. Mobile, and able to return for required treatments and study evaluations without undue hardship

8. Able to give Informed Consent

9. Able to understand and comply with the requirements of the trial

##### Exclusion Criteria

Study participants who meet any of the following criteria will not be eligible for participation in this study:

1. Unable or unwilling to wear compression bandage as directed

2. Evidence of severe liver disease, cardiac disease or chronic pulmonary disease

3. Medical condition likely to require systemic corticosteroids during the study period

4. Any significant condition that may preclude the participant from the study (e.g. severe depression or psychiatric illness)

5. Clinically suspected deep vein thrombosis

6. Unable or unwilling to attend clinic for routine treatment

7. Participation in this trial previously and/or who dropped out or were withdrawn

### Participant Consent

Informed consent will be taken according to ICH GCP (International Conference on Harmonization Good Clinical Practice). Before recruitment and enrolment into the study, each prospective participant will be given a full explanation of the nature and purposes of the study, and a copy of the Information Sheet to review. Once the essential study information has been provided, and the Investigator is assured that each study participant understands the implications of participating in the study, the participants will be asked to give consent to participate in the study by signing and dating the informed consent form A notation that written informed consent has been obtained, with date, will be made in the study participants source documentation and Case Report Form (CRF). The completed consent forms will be retained by the Investigator and a copy of the consent form will be provided to the study participant.

### Criteria for Participant Withdrawal

Participants will be advised that they may withdraw from the study at any time, for any reason, or if necessary, the Investigator may withdraw a study participant to protect their health. Study participants may also be withdrawn for not complying with study procedures such as not wearing compression bandages. The reasons for withdrawal will be fully documented in the study participants notes and CRF. Participants who are withdrawn or drop out of the randomised treatment will be allocated for continuing follow up care to the specialty wound clinic for wound management. All adverse events will be documented and the reasons for withdrawal ascertained wherever possible.

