### Plan and Trial Design

This pilot study is a randomised, multi-centre clinical trial to evaluate the efficacy and safety of graduated three layer straight tubular bandaging (intervention arm) compared with standard compression therapy (control arm) in participants with chronic venous ulceration. Neither participants nor study staff will be blinded to treatment. Screening evaluations will ensure that potential participants fulfil all requirements for entry into the study. Forty six study participants will be randomised (1:1) to either intervention arm or to the control arm of the study. Study participants will be reviewed weekly during the 12 week treatment period, and if healed in treatment period, participant will be also be reviewed monthly for three months during a subsequent follow up period.

In the following sections, a detailed description of all study procedures is given. All study visits and procedures are described and the evaluations performed at each visit are detailed. An overview and schedule of the visits and procedures is provided in Table 1.

**Table 1 T1:** Study Schedule

		Screening Period		Treatment Period Weeks													Follow-Up Period Months		
	
		Screening visit		Day 1	1	2	3	4	5	6	7	8	9	10	11	12	Month1	Month2	Month3
Informed Consent		X																	

Inclusion Criteria		X																	

Exclusion Criteria		X																	

Randomisation		X																	

Medical history		X																	

Physical Examination		X														X	X	X	X

Vital Signs		X		X	X	X	X	X	X	X	X	X	X	X	X	X	X	X	X

Intercurrent Illness		X		X	X	X	X	X	X	X	X	X	X	X	X	X	X	X	X

Intercurrent Medication		X		X	X	X	X	X	X	X	X	X	X	X	X	X	X	X	X

Tolerability Assessment				X	X	X	X	X	X	X	X	X	X	X	X	X	X	X	X

Target ulcer assessment		X		X	X	X	X	X	X	X	X	X	X	X	X	X	X	X	X

SF 36 and CWIS				X												X			X

Adverse events				X	X	X	X	X	X	X	X	X	X	X	X	X	X	X	X

Compression hosiery fitting/ application		X														X^2^			

Check for Ulcer Recurrence																	X	X	X

Care of ulcer information sheet		X														X^2^	X^4^	X^4^	X^4^

Referred back to specialty wound clinic																X^3^	X^4^	X^4^	X^4^

X^2^: If healed.

X^3^: If not healed.

X^4^: If ulcer has recurred.

*: If target ulcer has completely healed, (defined as 100% epithelialisation with no presence of exudate or scab).

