### Pilot study sample size justification

We will recruit 46 participants in total to enable the estimation of the between-person variability in percentage reduction in wound size from baseline to 12 weeks. There are insufficient previous studies to ascertain a likely value for this variability for use in power calculations for a fully powered trial.

The analysis principle for the primary outcome will be Intention-to-treat. The data will be analysed according to the treatment group to which participants are randomised even if they do not comply fully with their treatment. If participants drop out of the study they will be asked if they would still be prepared to return at the 12 week end of treatment schedule for target ulcer measurement.

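### Unblinded staff may withdraw participants for not wearing the bandage, and the week-12 recall is not worded to bring them back, so the primary outcome may be lost selectively

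*Protocol article*

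**What the plan says.** Criteria for Participant Withdrawal gives participants this advice: "they may withdraw from the study at any time, for any reason, or if necessary, the Investigator may withdraw a study participant". The ground named for the investigator's action is the participant's health. The next sentence adds a further ground: "Study participants may also be withdrawn for not complying with study procedures such as not wearing compression bandages". The section then says what follows: "Participants who are withdrawn or drop out of the randomised treatment will be allocated for continuing follow up care to the specialty wound clinic". It mentions no study measurement after that point.

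Plan and Trial Design states that "Neither participants nor study staff will be blinded to treatment". Participant Compliance says that wear is established by asking the participant.

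Pilot study sample size justification makes intention-to-treat the principle for the primary outcome: "The data will be analysed according to the treatment group to which participants are randomised even if they do not comply fully with their treatment". On people who leave, the same paragraph provides: "If participants drop out of the study they will be asked if they would still be prepared to return at the 12 week end". The purpose of that visit is to measure the target ulcer. No other provision in the article covers measurement after a participant leaves.

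**The concern.** Intention-to-treat fixes the arm in which a measured value is counted. It cannot supply a wound area that nobody measured. The people whom the analysis section promises to keep, those who do not comply fully, are the same people whom the withdrawal section allows staff to remove. The rule is discretionary, has no threshold, and is applied by staff who know the allocation.

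The loss need not be balanced. The Background, under Economic and personal burden of venous ulcers, says that the three-layer system (3L) "may improve potential for patients to tolerate and comply with wearing compression bandages". If non-wearers heal less well and are not measured, the arm that is worn less looks better than it would under intention-to-treat. If that arm is short stretch, the error widens the very difference the trial is sized on, a 50% reduction with standard compression against 20% with 3L. The 20% allowance for loss to follow-up protects the numbers and does nothing about selective loss.

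Two further results are affected. The third secondary outcome counts withdrawals as a measure of acceptability, and that count becomes partly a decision of unblinded staff. The pilot is also meant to estimate the variability of wound reduction for a larger trial, and losing non-wearers would tend to understate it.

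**Working it through.** **Plan's own figures** (Sample Size and Analysis plan). The design difference is ln(0.8/0.5) = 0.470. With SD 0.5, two-sided alpha 0.05 and 80% power, n = 2 × (1.960 + 0.842)² × 0.5² / 0.47² = 17.8, so 18 per group. Allowing 20% loss, 18/0.8 = 22.5, so 23 per arm. Both figures reproduce. The standard error of the difference at 18 per group is 0.5 × √(2/18) = 0.167.

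**Reading the text.** The withdrawal section names withdrawn participants and drop-outs as two groups, and so does exclusion criterion 7. The week-12 recall names only the second. Participant Compliance adds that participants treated in deviation from the protocol may be left out of the analysis, which pulls further away from intention-to-treat.

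**Illustration of bias.** All response and non-wear values here are assumptions.

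- Wearers have a 50% area reduction: W = ln(0.5) = −0.693.
- Non-wearers have a 10% reduction, N = ln(0.9) = −0.105, or a 35% reduction, N = ln(0.65) = −0.431.
- p is the share not wearing, all of them withdrawn: 20% in one arm and 10% in the other.
- r is the share of these who return at week 12: none or half.

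Full mean = (1−p)W + pN. Observed mean = [(1−p)W + prN] / [(1−p) + pr]. Shift = full − observed. Net shift = shift at p = 0.2 minus shift at p = 0.1.

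| Non-wearer reduction | Return at week 12 | Shift, p = 0.2 | Shift, p = 0.1 | Net | Share of 0.47 | Net in standard errors |
|---|---|---|---|---|---|---|
| 10% | none | 0.118 | 0.059 | 0.059 | 12.5% | 0.35 |
| 10% | half | 0.052 | 0.028 | 0.024 | 5.2% | 0.15 |
| 35% | none | 0.052 | 0.026 | 0.026 | 5.6% | 0.16 |
| 35% | half | 0.023 | 0.012 | 0.011 | 2.3% | 0.07 |

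With the same p, N and r in both arms the net shift is zero. As a harsher case, suppose the share lost differs by 20 percentage points and wearers do better than non-wearers by 0.25 to 0.47 on the log scale. The shift is then 0.20 × 0.25 = 0.05 to 0.20 × 0.47 = 0.094, or 11% to 20% of 0.47.

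**Variability.** Take SD 0.5 within wearers and within non-wearers. The full variance is 0.25 + p(1−p)d², where d is the gap between the two groups (0.588 or 0.262). The smallest case is p = 0.1, d = 0.262: 0.09 × 0.0686 = 0.0062, which is 2.5% of 0.25. The largest is p = 0.2, d = 0.588: 0.16 × 0.346 = 0.055, which is 22% of 0.25. If no non-wearer is measured, the pilot misses that part of the variance, even when loss is equal in both arms.

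**The case against.** The strongest reply is textual. The sentence on what happens next speaks of leaving the randomised treatment, so withdrawal may mean only stopping the allocated bandage. The week-12 recall follows directly after the sentence on non-compliers, so its reference to dropping out may be meant to cover everyone who leaves. Both readings are possible. Neither is secured, because the protocol elsewhere lists the two groups separately, and on either reading no week-12 measurement is fixed for a participant withdrawn by staff. Sites could apply the rule differently.

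A second reply is that a condensed article need not carry every procedure. That is fair for the missing detail. The discretionary withdrawal rule, however, is stated in the article and sits badly with the stated analysis principle.

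Some mitigation is real. People unwilling to wear compression are excluded at entry. Episodes of non-compliance are to be recorded with their duration, which implies that they do not always end participation. Participants come from the wound clinics to which they would return, so recall is practicable. Recall can never be compulsory.

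The illustration is also assumed and small, and it gives 3L wearers a 50% reduction where the plan expects 20%. That last point does not shrink the bias if short stretch is the less-worn arm. With a 20% reduction in 3L wearers, 10% in all non-wearers and none returning, the 3L shift falls to 0.1 × ln(0.9/0.8) = 0.012, and the net becomes 0.118 − 0.012 = 0.106. What stands is that both size and direction are unknown.

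**Conclusion.** The concern holds. The protocol allows unblinded staff to withdraw non-wearers and makes no clear provision to measure their ulcers at week 12, although its primary analysis is meant to include them. Under the tabulated assumptions the resulting bias is modest: 0.01 to 0.06 on the log scale, or 0.07 to 0.35 standard errors. It rests on unequal non-wear, on withdrawal of every non-wearer and on poorer healing in non-wearers, none of which the document quantifies. It vanishes if loss and response are equal in the two arms. The matter should be fixed because a week-12 area that was not taken cannot be recovered at analysis and the remedy is cheap. Confidence is medium, because the wording is open to a more favourable reading.

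**What to change.** In Criteria for Participant Withdrawal, state that not wearing or stopping the allocated bandage does not end the scheduled target-ulcer assessments to week 12 unless the participant withdraws consent. Whether the bandage should be stopped remains a clinical decision.

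In Pilot study sample size justification, extend the week-12 recall to participants who drop out or are withdrawn.

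Record non-wear under self-reported compliance (secondary outcome 6), and stopping the bandage, with its reason, under acceptability (secondary outcome 3). The acceptability outcome then no longer depends on whom staff choose to remove.

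The cost is a protocol amendment during recruitment; Current study status reports 25 of the 46 participants recruited. The assessments are already in the weekly schedule, so no new procedure is needed. At the assumed 10% to 20% non-wear, the extra work is the remaining assessments for 23 × 0.1 = 2.3 to 23 × 0.2 = 4.6, or about 2 to 5 participants per arm.
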